### 2.7.A. SAMPLE SIZE CALCULATION AND POWER

Power was calculated for the overall primary study endpoint (change in VACS index score). Power calculations assumed a two-sided hypothesis test, with a significance level of 0.05. It was expected that 250 participants would be enrolled into the study. We anticipated 20% loss to follow-up due to death and participant withdrawal. Based on the VACS study, the standard deviation of the change in VACS index score from initiation of ART to after one year was 25. We expect the standard deviation will be similar in this study. Given these assumptions and with 200 evaluable participants (assuming 20% loss to follow-up, and 100 participants in each arm), the study is anticipated to have 80% power to detect a difference between the placebo and zinc groups in their mean changes in VACS index score over the 18-month period as small as 10 (e.g. 20 vs. 10 for the placebo and zinc groups, respectively) using a two-sided t-test.

Aim 2: To test the efficacy of zinc supplementation compared to placebo to slow HIV disease progression as measured by CD4 cell count. We anticipate analyzing log transformed values of change in CD4 cell count due to possible skewness in the data. Group differences will be back transformed from the natural log scale and therefore the parameter of interest is the ratio of the mean changes in CD4 cell count from baseline to 18 months for the zinc group relative to the placebo group, where change is defined as CD4 count at baseline - CD4 count at 18 months. The estimated coefficient of variation for the change in CD4 cell count from baseline to 18 months (baseline - 18 months) is 0.20 cells/ $\mu$ L. Given these assumptions, with 200 evaluable participants (100 in the zinc and placebo arms), the study will have 96.3% power to detect a ratio of 0.90 (zinc:placebo) between the mean changes of CD4 counts for the zinc and placebo groups using a two-sided t-test.

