#### 4.5 Baseline Participant Characteristics

Descriptive statistics will be calculated for the following variables at baseline overall and stratified by randomized group: age, sex, heavy alcohol (past week), education, marital status, employment, VACS Index, CD4, Reynolds risk score, IL-6, D-dimer, sCD14, 16sRDNA , smoking status (current, ever, never), BMI, CVD, AST/ALT, FIB4, HCV (test), HVL, hemoglobin, platelets, eGFR, Blood pressure, Total cholesterol, HDL cholesterol, CRP, mother/father MI. For continuous variables, the following will be provided: median, mean, standard deviation, 0th, 25th, 50th, 75th, and 100th percentiles. For categorical variables, frequencies and proportions will be provided. For each primary and secondary outcome, descriptives will also be reported stratified by arm and follow-up time, (note, no testing will be done for any of the above).

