#### 5.2 Analysis Methods

The study aims to test the hypothesis that compared with placebo, participants receiving zinc supplementation will have significantly 1) lower VACS index scores; 2) higher CD4 cell counts; 3) lower Reynolds risk score and; 4) lower biomarker levels of microbial translocation and inflammation. The primary outcome is improved markers of mortality, as measured by change in VACS index score between baseline and 18 months. The secondary outcomes are slower HIV

disease progression, as measured by change in CD4 cell count; improved markers of AMI risk, as measured by the Reynolds Risk Score; and lower biomarker levels of microbial translocation and inflammation.

This study will be conducted under the intention-to-treat principle and thus main analyses will include all participants according to their randomized assignment. Descriptive statistics will be calculated for variables at baseline and each follow-up time point. At baseline, participant characteristics will be presented by randomized arm to assess whether there are any differences between groups. Spearman correlation coefficients will be obtained to identify pairs of variables that may be collinear ( $r > 0.4$ ) and would therefore not be included together in regression analyses.

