The main analysis evaluating the impact of zinc on the primary study outcome (i.e., change in VACS index) will use multiple regression models that include randomization group (i.e., zinc vs. placebo) as the main independent variable. The regression analyses will control for the two block randomization stratification factors: heavy alcohol consumption during the past week and gender. In addition, the models will control for baseline characteristics that differ between groups in order to avoid confounding. Potential confounders of interest, measured at baseline, include demographics, past month alcohol use, age, gender, anti-inflammatory medication use, cardiovascular disease risk factors, HCV status, substance use (e.g., alcohol, smoking, cocaine), CD4 cell count, HIV-1 RNA, duration of awareness of HIV infection, and socioeconomic status. If the data are normally distributed, multiple linear regression models will be used. However, if the distribution is skewed, transformations of the data will be performed (e.g., log transformation). If an appropriate transformation is not identified, a median regression model will be used. The secondary outcomes, including HIV disease progression, as measured by change in CD4 cell count (Aim 2); the Reynolds risk score (Aim 3); and biomarkers of microbial translocation and inflammation (Aim 4) will be analyzed using the same approach described above. A secondary analysis will be conducted using a per protocol approach that includes only those participants who were adherent with their assigned intervention (i.e., taking zinc or placebo 80% of the time).

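### The SAP adds covariates to the primary and secondary models when the arms look different at baseline, with no criterion, instead of fixing a prognostic list that includes the baseline outcome

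*Supplement*

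**What the plan says.** SAP 5.2 puts three terms in the primary model in every case: randomised group, gender and past-week heavy drinking. Beyond these, "the models will control for baseline characteristics that differ between groups in order to avoid confounding". A list of potential confounders follows. It has about a dozen entries, some of them open classes such as demographics and cardiovascular risk factors. Baseline CD4 count and HIV-1 RNA are named; the baseline VACS index is not.

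SAP 5.2 says that characteristics will be shown by arm so that differences can be assessed. SAP 4.5 says of its baseline descriptives: "note, no testing will be done for any of the above". Neither section says how large a difference must be to count.

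SAP 5.2 also states: "Spearman correlation coefficients will be obtained to identify pairs of variables that may be collinear". The cut-off is r above 0.4, and such pairs are not entered together. Which member stays is not stated.

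The same approach applies to CD4 change, the Reynolds score and the biomarkers. Protocol 8.1 has the same text. SAP 2.6 places the analysis after the 18-month data are collected and cleaned. No section says when, or by whom, the covariate set is fixed.

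**The concern.** The stated purpose is to avoid confounding. With 1:1 randomisation (Protocol 3.2), baseline differences between the arms arise by chance. What decides whether adjustment helps is how well a covariate predicts the outcome, and the rule does not ask that.

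Two consequences follow. First, the primary model cannot be written down until baseline data have been seen by arm, and two analysts following the SAP could fit different models. Second, a good predictor that happens to be balanced can be left out, and the precision it would have given is lost. The clearest case is the baseline value of the outcome. For the Reynolds score and the biomarkers the outcome in SAP 5.1 is the 18-month level, so baseline would enter only if judged to differ between arms.

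The r > 0.4 screen adds another open choice. Correlation among adjustment covariates does little harm to the treatment coefficient in a randomised comparison, so the screen is not needed for that estimate.

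**Working it through.** **Inputs from Protocol 2.7.A.** Two-sided 0.05; 100 evaluable per arm; SD: "the standard deviation of the change in VACS index score from initiation of ART to after one year was 25"; detectable difference "as small as 10 (e.g. 20 vs. 10 for the placebo and zinc groups, respectively) using a two-sided t-test".

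**Plan's own figure.**
- Standard error = 25 × √(2/100) = 3.54, and 10/3.54 = 2.83.
- Normal power = Φ(2.83 − 1.96) = 80.7%; noncentral t gives 80.4%.
- The required size is 99 per arm, and 198/0.8 = 247.5, so 248 against 250 planned. The stated 80% reproduces.

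**Chance of a trigger.** Assume 12 independent candidates and p<0.05 as the meaning of a difference. The chance that at least one qualifies is 1 − 0.95¹² = 46%.

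**Power with fixed prognostic covariates.** Residual SD = 25 × √(1 − R²). The documents give no R², so it is varied.
- R² 0.10: SD 23.7, power 84.6%
- R² 0.25: SD 21.7, power 90.4%
- R² 0.40: SD 19.4, power 95.5%
- R² 0.50: SD 17.7, power 97.9%

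**Plausible R² for baseline VACS.** Assume equal variances at baseline and 18 months, with correlation ρ. The covariance of change with baseline is −(1 − ρ)σ², and the variance of change is 2(1 − ρ)σ². So R² = (1 − ρ)/2, which is 0.15 at ρ = 0.7 and 0.25 at ρ = 0.5.

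**Simulation of the written rule.** There were 6,000 trials per row, with n = 200 and complete data. The two stratification factors were always in the model. Of 12 candidates, three were prognostic and shared R², and three others correlated 0.6 with those. Assumptions that the SAP does not supply: the trigger is p<0.05, and within a pair correlated above 0.4 the more imbalanced covariate stays. The last column takes the smallest p-value from four covariate sets: none added, or those differing at p<0.05, p<0.10 or p<0.20. Monte Carlo standard error is about 0.3 points for type I error and at most about 0.5 for power.

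| Assumed R² | Power, rule | Power, prespecified | Type I, rule | Type I, prespecified | Type I, best of four |
|---|---|---|---|---|---|
| 0 | 79.4% | 79.2% | 4.8% | 4.7% | 5.7% |
| 0.10 | 80.0% | 83.9% | 4.5% | 5.3% | 6.2% |
| 0.25 | 80.8% | 89.1% | 4.2% | 4.8% | 6.7% |
| 0.40 | 82.3% | 95.4% | 4.1% | 5.4% | 7.1% |
| 0.50 | 82.6% | 97.5% | 3.1% | 4.7% | 6.2% |

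A simpler simulation, with one covariate, the same trigger and 4,000 trials, shows the same pattern. At R² 0.2, 0.3 and 0.4, power under the rule is 82.1%, 81.6% and 81.4%, against 88.0%, 91.8% and 94.8% with constant adjustment. Type I error under the rule is 4.4%, 4.0% and 3.6%.

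**The case against.** The strongest reply is that nothing promised is lost. The 80% rests on an unadjusted t-test, and the rule delivers about that. The two stratification factors are always in the model, the candidates are largely named, and the trigger uses baseline data rather than outcomes. The sizes above depend on an R² and a threshold that the documents do not contain, and the benefit vanishes at R² = 0. All of this stands, and it limits the point to forgone precision and incomplete prespecification.

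Four stronger readings are tempting, and the documents do not support them.
- **The trial falls short of its planned power.** It does not. Simulated power under the rule is 79.4% to 82.6%, within Monte Carlo error of the stated figure or above it.
- **The rule inflates false positives.** Applied mechanically, it is at or below 5%. Values above 5% need an analyst to try several covariate sets and report the most favourable. No passage describes that; the text merely leaves room for it.
- **SAP 4.5 and 5.2 contradict each other.** Imbalance can be judged by size without a test, so both sections can be followed. What is missing is the criterion.
- **Correlated covariates are thrown out.** Only joint entry is barred, so one of each pair can stay and will carry part of the other's information. The gap is that no rule says which one stays.

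The reply does not remove the central point. Choosing covariates by chance imbalance is a weaker method than choosing them by prognostic value, and a better one is available at almost no cost.

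**Conclusion.** The point holds as a weakness of method and prespecification in the primary and secondary models. No other section mends it.

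On the planning SD of 25, 100 evaluable per arm and a p<0.05 trigger, the rule forgoes about 4 points of power at R² 0.10, 8 at 0.25 and 13 at 0.40 against a prespecified prognostic set. At R² = 0 it forgoes nothing. R² of 0.10 to 0.25 is plausible from baseline VACS alone, under the equal-variance assumption.

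For R² up to 0.40, type I error under the mechanical rule is about 3.6 to 5% across the two simulations; the one run at R² 0.50 gave 3.1%. Discretionary choice among four covariate sets gives 5.7 to 7.1%. That shows what the wording permits and is no evidence of what was done. This is a cheap improvement that should be made, and it is not a threat to the design.

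**What to change.** Replace the imbalance rule in SAP 5.2, and the matching text in Protocol 8.1, with a fixed covariate list for all primary and secondary models:
- gender and past-week heavy drinking;
- the baseline value of the outcome, where collected;
- age;
- a short named list taken from the SAP's own candidates, chosen for expected prognostic value by someone without sight of arm-level data.

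State that these enter whatever the baseline balance. Remove the r > 0.4 exclusion from the treatment-effect models. Any model driven by observed imbalance can stay as a labelled sensitivity analysis, with its criterion written down.

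The cost is a change of wording and a few degrees of freedom out of about 200. If the covariates prove unrelated to the outcome, the loss is negligible, as the R² = 0 row of the simulation shows.

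### The primary model is chosen from the observed VACS distribution without a stated criterion, so the tested parameter is not fixed as the powered difference in mean change

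*Supplement*

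**What the plan says.** SAP 5.2 (repeated in Protocol 8.1) sets a three-step sequence for the primary outcome, change in VACS index from baseline to 18 months. Linear regression is used if the data are normal. If not, "However, if the distribution is skewed, transformations of the data will be performed (e.g., log transformation"). Finally, "If an appropriate transformation is not identified, a median regression model will be used". The secondary outcomes follow the same approach.

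SAP 5.3 makes the multiple-imputation model the primary ITT analysis but does not settle the regression form or the scale. SAP 2.6 places all outcome analyses after the 18-month data have been collected and cleaned.

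Protocol 2.7.A, to which SAP 2.3 refers, claims "80% power to detect a difference between the placebo and zinc groups in their mean changes in VACS index score". The difference is stated to be "as small as 10 (e.g. 20 vs. 10 for the placebo and zinc groups, respectively) using a two-sided t-test".

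**The concern.** The sequence has a qualitative trigger (normal or skewed) but does not say:

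- how normality or skewness is judged, or at what cut-off;
- whether raw changes or model residuals are examined;
- which transformations are allowed, and what makes one suitable;
- how changes at or below zero are handled;
- whether the decision is taken before treatment codes are linked to outcomes.

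Two analysts could follow this text on the same data and report different effect measures. Only one of those measures is the quantity the trial was sized for. The log named as the example cannot be applied directly to a change score that takes both signs. At stake is whether the primary result can be read as the prespecified test of the difference in mean VACS change.

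**Working it through.** **Inputs, all from Protocol 2.7.A.** Two-sided α = 0.05; SD of change 25 ("the standard deviation of the change in VACS index score from initiation of ART to after one year was 25"); difference 10, with arm means 20 (placebo) and 10 (zinc) given as an example; 100 per arm ("with 200 evaluable participants (assuming 20% loss to follow-up, and 100 participants in each arm").

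**1. The plan's own power.** SE = 25 × √(2/100) = 3.536, and 10/3.536 = 2.828. Normal approximation: Φ(2.828 − 1.960) = 80.7%. Noncentral t with 198 df: 80.4%. The stated 80% reproduces, for a difference in means.

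**2. What each branch estimates.**

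| Branch in SAP 5.2 | Parameter for arm | Powered in 2.7.A? |
|---|---|---|
| Linear regression | Difference in mean change | Yes |
| Transformed outcome | Difference on the transformed scale (a ratio under log) | No |
| Median regression | Difference in median change | No |

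The mean and median differences coincide if zinc shifts every participant's change by the same amount. They need not coincide if it alters the shape of the distribution.

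**3. Does a plain log fit the outcome?** Take change as 18 months minus baseline and assume normality for illustration. P(change ≤ 0) = Φ(−mean/SD).

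| SD | Placebo (mean 20) | Zinc (mean 10) |
|---|---|---|
| 15 | 9.1% | 25.2% |
| 20 | 15.9% | 30.9% |
| **25 (plan)** | **Φ(−0.80) = 21.2%** | **Φ(−0.40) = 34.5%** |
| 30 | 25.2% | 36.9% |

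At SD 25 the average over both arms is (21.2 + 34.5)/2 ≈ 27.8%. The plan does not define the sign of the VACS change. With baseline minus 18 months, the direction that 2.7.A uses for CD4, the log would be undefined for 100 − 21.2 = 78.8% and 100 − 34.5 = 65.5%. Under either sign, a plain log would leave out a large share of participants.

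**4. Power if median regression were used on near-normal data (illustrative).** Relative efficiency is 2/π = 0.637. Then 2.828 × √0.637 = 2.257, and Φ(2.257 − 1.960) = 61.7%; the noncentral t gives about 61%. The rule as written sends near-normal data to linear regression, so this is not a forecast for the trial. With heavy tails the comparison could reverse.

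**5. Type I error when the rule is followed.** The rule was simulated under the null with 100 per arm and 1,500 runs per distribution. Assumptions: a skewness test on arm-centred residuals as the gate, no covariates, and no transformation step. Rejection rates were 5.7% (normal), 3.3% (gamma, shape 4), 6.3% (exponential) and 4.5% (t, 4 df). Least squares alone gave 4.8% to 5.7%. In the exponential case the gate fired every time, so the 6.3% is the error rate of median regression itself and not an effect of selection.

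**The case against.** The strongest reply is that this is an ordered rule driven by the shape of the data, not by the treatment estimate or p-value. Normal data go to the powered model, log is only an example, shifted or sign-preserving transformations fit the wording, and median regression is a stated fallback. The paragraph also covers biomarkers and the Reynolds score at 18 months, for which a log is natural.

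Much of this stands. A reader might infer that the plan breaks down for a fifth to a third of participants. It does not: those shares assume normality, under which the log branch is not reached, and they use arm means given only as an example. A reader might also infer that power falls from 80% to 61%, but that needs median regression in a case the rule sends elsewhere. Finally, a reader might infer an inflated primary p-value. The simulation shows none attributable to selection. Taking the smaller of two p-values would inflate the error, but the plan does not provide for that.

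The reply does not fix the parameter. A shifted log needs a constant, none is given, and the result depends on it. The fallback keeps the analysis feasible by moving to another parameter. A numeric trigger or a decision blind to arm would close the gap in procedure, but the data would still decide whether the powered quantity is tested.

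**Conclusion.** The point holds as a gap in prespecification. The reported effect measure depends on the observed outcome through undefined criteria, and only one of the three branches matches the quantity powered in Protocol 2.7.A. This follows from the text alone and needs no distributional assumption.

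The figures are illustrations. The 21% and 34% rest on normality, the example means and SD 25; they show that the named log does not suit a signed change score. The 61% applies only to median regression on near-normal data. The documents support no claim that power will be lost or that the type I error is inflated when the rule is followed.

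The data-driven choice is also unnecessary. With about 100 per arm, least squares with robust standard errors supports inference on the mean difference without normality.

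**What to change.** In SAP 5.2, prespecify the primary analysis as linear regression of VACS on arm, the two stratification factors and baseline VACS, with robust (for example HC3) standard errors, whatever the distribution. With baseline VACS in the model, the 18-month value and the change give the same arm coefficient, so either can be the outcome; state which, and define the sign of change. Fit this model in the imputed data sets that SAP 5.3 makes primary.

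Keep median regression as one named sensitivity analysis. For the positive, skewed 18-month secondary outcomes (IL-6, D-dimer, sCD14, IFABP, LBP, Reynolds score), fix the log scale in advance and adjust for the log baseline value where it was measured.

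The cost is SAP wording only: no new data, visits or participants, since the trial already collects baseline VACS. The downside is small: some efficiency may be lost if VACS change is heavy-tailed, and the median sensitivity analysis would help to show that.

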### 5.3 Missing Data

Enrollment and Attrition/Missing data: Participants who meet eligibility criteria and agree to participate will be compared with subjects who were determined to be eligible but declined enrollment on data captured during eligibility assessment. The 2 independent samples t-test and Fisher's exact test will be used to test for statistically significant differences between subjects who enroll and those who do not, and to test for significant differences between subjects lost to follow-up and those who complete it. Missing data patterns will be evaluated including the frequency and percentage of subjects missing for each variable and the distribution of the number of variables missing for subjects. In addition, data collected to the point of lost to follow-up will be compared to the data of those who complete the study to examine missing data mechanisms, e.g., missing completely at random (MCAR), missing at random (MAR), or not missing at random (NMAR). We will consider various approaches to account for missing data such as multiple imputation methods and likelihood-based approaches, if needed. In situations where missing data occurs, we will document the reasons for the missing data whenever possible. The proposed study has accounted for a 20% random noninformative loss to follow-up and will still have sufficient power with this potential loss in size. Multivariate multiple Imputation using iterative Markov Chain Monte Carlo (MCMC) method will be used to account for missing data. This model is the primary ITT analysis.

### 5.4 Additional Analyses

Effect of zinc over time: The main analyses will focus on the VACS index, our primary outcome, and other secondary outcomes at the 18 month time point as the primary interest is in evaluating the long-term effects of zinc and it is anticipated that effects will change over time. Additional analyses using generalized linear mixed effects models will be used to incorporate the repeated measures for each outcome in the same model and will test for possible zinc by time interactions (e.g. does the effect of zinc increase over time). The mixed effects models will include subject-specific

random intercepts and slopes to account for the correlation due to having repeated observations for each subject. The mixed models will be implemented in SAS PROC MIXED. In addition to the mixed effects model, we will also consider additional confirmatory models such as the general linear model for correlated data using an autoregressive covariance structure. We will use  $\alpha=.10$  to explore interaction. If the interaction is significant (i.e.  $p<0.10$ ), subsequent stratified analyses will be conducted.

